## 2. Aim and Objectives

This study aims to evaluate the effectiveness and safety of the combination of varenicline and NRT lozenges at assisting achievement of abstinence amongst heavy smokers admitted to six 'smoke-free' public hospitals in Australia.

The primary objective of the study is to compare biochemically-verified continuous abstinence in hospitalised smokers treated using varenicline plus NRT lozenge versus varenicline monotherapy.

The secondary objectives of this study are to compare:

- Self-reported 7-day point prevalence abstinence and continuous abstinence in the two treatment arms from 2 weeks to 3, 6 and 12 months after treatment initiation
- CO verified 7-day point prevalence abstinence at 6 and 12 months from treatment initiation for participants who self-report abstinence at these follow-ups
- Self-reported treatment adherence and adverse events to the study medicines at all follow-ups as well as the number of Quitline sessions attended after treatment initiation

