### 4.2 Data Analysis

Data will be stored in a suitable database (e.g. REDCap™, ACCESS™) and exported for analysis in Statistical Package for Social Sciences (SPSS) (version 23.0; IBM, Armonk, NY) and Stata (ver 15, StataCorp, College Station, TX). As recommended by the Russell Standard, all randomised patients will be accounted for in the intention to treat (ITT) analysis. Participants with missing outcomes at follow-up or whose self-reported abstinence was not biochemically validated will be considered as smokers. Sensitivity analyses using multiple imputation methods will also be carried out. Deceased participants will be excluded from

analyses. In a supportive analysis of the primary efficacy endpoint, an analysis will also be conducted on the per protocol set, which excludes patients with any major protocol deviations.

Logistic regression analyses will be used to examine the efficacy of intervention on the primary outcome, after testing homogeneity between hospitals using a random effects meta-analysis. In the event of heterogeneity, a more robust model incorporating clustering by hospital will be fitted. The effect of intervention on continuous abstinence at 6 months will be tested in pre-specified subgroups (per hospital, nicotine dependence, highly motivated versus moderately motivated smokers and men versus women) using models fitted for each subgroup containing main effects for intervention and subgroup and an interaction between them. Statistical significance will be considered at a two-sided p value of 0.05.

All randomised participants who take at least one dose of the treatment medications will be included in the safety analysis. A chi-squared test will be done to compare the frequency of treatment withdrawal between the treatment and comparator arms. The number of participants discontinuing treatment prematurely for any reason will be summarised by treatment group and by reasons for discontinuation.

The incidence of all suspected adverse events will be summarised by treatment group under the following categories: type, severity, action taken and outcome. Severity of adverse events will be reported using the CTEAE grading scale (v5.0). The causality of the adverse events will be determined using the Noranjo algorithm.

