Deceased participants at each time-point will be excluded from those specific analyses. All analyses will be adjusted for baseline HSI score.

HSI and PHQ-9 score differences from baseline to 3, 6 and 12 months will be compared between the treatment groups using Mann-Whitney U tests.

**Table 3: Heaviness of Smoking Index and Patient Health Questionnaire-9 score differences from baseline to 3, 6 and 12 months**

| Outcome          | Baseline     |         | 3-months     |         | 6-months     |         | 12-months    |         |
|------------------|--------------|---------|--------------|---------|--------------|---------|--------------|---------|
|                  | Intervention | Control | Intervention | Control | Intervention | Control | Intervention | Control |
| HSI score |              |         |              |         |              |         |              |         |
| HSI score | ----         | ----    |              |         |              |         |              |         |

|                                                   |      |      |  |  |  |  |  |  |
|---------------------------------------------------|------|------|--|--|--|--|--|--|
| (% participants showing improvement) † |      |      |  |  |  |  |  |  |
| PHQ-9 score                                       |      |      |  |  |  |  |  |  |
| PHQ-9 score (% participants showing improvement)  | ---- | ---- |  |  |  |  |  |  |

860 \*Indicates significant differences ( $p < 0.05$ ) between the intervention and control groups. †Follow-up score  
861 lower than baseline score indicates improvement

862  
863  
864  
865  
866  
867

868 A data safety and monitoring board (DSMB) provided oversight of adverse event data on a  
869 periodic basis. For the primary safety outcome, the proportion of reported adverse events  
870 occurring between treatment initiation and over 12-month follow-up will be compared  
871 between the treatment groups using a  $\chi^2$  test or Mann-Whitney U tests, as appropriate.

872 **Table 4: Adverse events experienced by treatment group**

| Outcome                                                              | Intervention | Control | P-value |
|----------------------------------------------------------------------|--------------|---------|----------------|
| Adverse events experienced at week 1 * , n (%)            |              |         |                |

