| Adverse events experienced at week 1 * , Median and IQR   |              |         |                |
| Adverse events experienced at week 2 † , n (%)            |              |         |                |
| Adverse events experienced at week 2 † , Median and IQR   |              |         |                |
| Adverse events experienced at 3-months ‡ , n (%)          |              |         |                |
| Adverse events experienced at 3-months ‡ , Median and IQR |              |         |                |

|                                                                         |  |  |  |
|-------------------------------------------------------------------------|--|--|--|
| Adverse events experienced at 6-months § , n (%)             |  |  |  |
| Adverse events experienced at 6-months § , Median and IQR    |  |  |  |
| Adverse events experienced from week 2 to 6-months # , n (%) |  |  |  |

873

874

875 **Table 5: Adverse events experienced by treatment group at 1-week, 2-week, 3-months and 6-months**

| Adverse events                    | 1-week * |         | 2-week † |         | 3-months ‡ |         | 6-months § |         | Overall # |         |
|-----------------------------------|---------------------|---------|---------------------|---------|-----------------------|---------|-----------------------|---------|----------------------|---------|
|                                   | Intervention        | Control | Intervention        | Control | Intervention          | Control | Intervention          | Control | Intervention         | Control |
| Nausea                            |                     |         |                     |         |                       |         |                       |         |                      |         |
| Vomiting                          |                     |         |                     |         |                       |         |                       |         |                      |         |
| Indigestion                       |                     |         |                     |         |                       |         |                       |         |                      |         |

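### The primary safety outcome is compared between arms only by a p-value, with no effect estimate or confidence interval, and Table 4 has no row for the window that defines it

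*Combined protocol and SAP*

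**What the plan says.** Safety is part of the stated aim. Protocol section 2 begins: "This study aims to evaluate the effectiveness and safety of the combination of varenicline and NRT lozenges".

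The SAP paragraph before Table 4 names a primary safety outcome: "For the primary safety outcome, the proportion of reported adverse events" "occurring between treatment initiation and over 12-month follow-up will be compared" between the arms, by a chi-squared "test or Mann-Whitney U tests, as appropriate". The table that follows, "Table 4: Adverse events experienced by treatment group", has three columns: intervention, control and p-value. Its rows are n (%) or median and IQR at single visits, plus one cumulative row, "Adverse events experienced from week 2 to 6-months". Table 5 breaks events down by type and arm and has no comparative statistic.

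Protocol section 4.2 plans for stopping treatment: "A chi-squared test will be done to compare the frequency of treatment withdrawal between the treatment and comparator arms". The same section sets the threshold: "Statistical significance will be considered at a two-sided p value of 0.05".

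The main efficacy tables, SAP Tables 2 and 6, do carry odds ratios with 95% confidence intervals.

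**The concern.** The safety question is how many more adverse events, if any, come with adding nicotine lozenges to varenicline. That question needs an estimate of size with its uncertainty. As planned, the only statistic that compares the arms is a p-value, which shows neither the size of a difference nor the largest excess still compatible with the data.

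An excess is plausible on the protocol's own terms. Appendix C lists nausea, vomiting, indigestion, constipation, headache and insomnia under both products, with nausea above 1 in 10 for the lozenge. The 160 per arm was chosen for a 15-point difference in abstinence, and neither document states power, a margin or a target precision for harm. A non-significant safety result could then sit beside a sizeable true excess without the report showing it.

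The defined outcome also has no place in the shells. It runs from treatment initiation to 12 months, while the longest Table 4 row starts at week 2 and ends at 6 months.

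**Working it through.** **Inputs.** From the documents: 160 per arm (protocol section 4.1; SAP sample size), 1:1 allocation (section 3.3), two-sided 5% (section 4.2), and a safety set of randomised participants with at least one dose (section 4.2), so at most about 160 per arm. Assumed: the control proportion with an adverse event, which the documents do not give and which is varied from 5% to 85%, and a true excess of 10 points, used as an illustration.

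**Step 1: reproduce the plan's own figure.** For 23% v 38% with 80% power:

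n' = [1.96·√(2·0.305·0.695) + 0.8416·√(0.23·0.77 + 0.38·0.62)]² / 0.15² = (1.276 + 0.541)² / 0.0225 ≈ 146.7, that is 147.

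With continuity correction: n = (n'/4)·[1 + √(1 + 4/(n'·0.15))]² = (146.7/4)·(2.087)² ≈ 159.8, that is 160. The stated size is reproduced, and it is an efficacy calculation only.

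**Step 2: chance that the chi-squared test misses a 10-point excess.** With p2 = p1 + 0.10 and p̄ their mean:

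power ≈ Φ{[0.10 − 1.96·√(2p̄(1−p̄)/160)] / √([p1(1−p1) + p2(1−p2)]/160)}

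Example, 20% v 30%: (0.10 − 1.96·0.0484)/0.0481 = 0.106, so power is 54.2% and the miss rate is 45.8%. Exact enumeration of the two binomials, without continuity correction, gives 45.3%.

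**Step 3: 95% CI half-width for the risk difference,** if both arms show the control rate p: 1.96·√(2p(1−p)/160).

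| Control rate | With excess | Missed, normal approx. | Missed, exact | CI half-width, points |
|---|---|---|---|---|
| 5% | 15% | 15.0% | 13.2% | 4.8 |
| 10% | 20% | 29.1% | 28.6% | 6.6 |
| 20% | 30% | 45.8% | 45.3% | 8.8 |
| 30% | 40% | 53.4% | 53.0% | 10.0 |
| 40% | 50% | 56.5% | 56.6% | 10.7 |
| 50% | 60% | 56.5% | 56.6% | 11.0 |
| 60% | 70% | 53.4% | 53.0% | 10.7 |
| 70% | 80% | 45.8% | 45.3% | 10.0 |
| 80% | 90% | 29.1% | 28.6% | 8.8 |
| 85% | 95% | 15.0% | 13.2% | 7.8 |

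The exact figure at 85% follows from the 5% row by symmetry. With Yates correction the miss rate is 51% to 61% for control rates of 20% to 70%. The same table applies to treatment withdrawal: 10% v 20% is missed 29% of the time.

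**Step 4: what an interval would show.** Suppose 96/160 (60%) in control and 110/160 (68.75%) in intervention have an event. The difference is 8.75 points. The pooled proportion is 206/320 = 0.644, so z = 0.0875/√(2·0.644·0.356/160) = 0.0875/0.0535 = 1.63, not significant. The unpooled SE is √(0.60·0.40/160 + 0.6875·0.3125/160) = 0.0533, and the 95% CI is 8.75 ± 10.45, that is −1.7 to +19.2 points. The p-value column would show no significant difference, while the interval would show that an excess of up to 19 points is not excluded.

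The Mann-Whitney option was not evaluated, because the documents give no distribution of event counts.

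**The case against.** The strongest reply is that safety is not judged by this p-value alone. Section 4.2 plans summaries by type, severity, action taken and outcome, causality grading, and discontinuations by reason. Section 6 adds adjudication of serious events and DSMB review. Table 4 prints n (%) by arm, from which a reader could compute a difference and interval. All of this stands, so it would be wrong to call the p-value the plan's only safety evidence. But none of these items gives a between-arm estimate with its uncertainty. The reader's own calculation also fails for the defined outcome, because no row covers initiation to 12 months, and rows of medians yield no interval for a risk difference.

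A reader might also infer that a non-significant result will be reported as showing the combination to be safe. The documents set no such rule and make no equivalence or non-inferiority claim for safety, so that would be a prediction about a later report, not a reading of the plan.

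Nor is the lack of power for harm a breach of anything. The 80% target applies to abstinence only, and trials are seldom sized for adverse events. Eighty per cent power for a 10-point excess would need 199 per arm at control rates of 10% or 80%, and up to 392 at 45%. The remedy is an interval, not a larger trial.

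**Conclusion.** The point stands as a cheap improvement. For the primary safety outcome and for treatment withdrawal, the sole planned comparative statistic is a test result, without an effect estimate or interval, and the primary safety outcome has no row in its table.

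The size depends on an assumed control rate. With 160 per arm, the uncorrected chi-squared test misses a true 10-point excess 45% to 57% of the time if the control rate lies between 20% and 70%. The figure falls to 29% at 10% or 80%, and to 13% at 5% or 85%. Missing the excess about half the time is therefore not an unconditional property of the design: both arms take varenicline and many event types are listed, so a high any-event rate, where the miss rate is lower, cannot be ruled out. What holds over the 20% to 70% range is that a non-significant p-value alone could not exclude a 10-point excess.

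**What to change.** In the SAP safety paragraph and Table 4:

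1. Define the primary safety outcome as the proportion of participants with at least one adverse event from treatment initiation to 12 months. The present wording leaves open whether events or participants are counted.
2. Add that row to Table 4 and state its denominator. Section 3.8.5 does not name adverse events among the 12-month items, although section 2 plans them at all follow-ups, and participants recruited before the extension are called at 12 months only if they consent. Confirm what is collected, and say how people without a 12-month contact are counted.
3. Report the risk difference (intervention minus control) with a 95% CI for this outcome and for treatment withdrawal. The p-value may stay beside it.
4. State that a non-significant difference will not be interpreted as equal safety, and that the safety conclusion will cite the upper confidence limit as the largest excess not excluded.

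The cost is SAP wording, one table row and one column. If 12-month adverse events are collected as section 2 intends, no new data, patients or visits are needed. The downside is a less favourable safety statement: the upper limit will lie about 9 to 11 points above the observed difference at event rates of 20% to 80%.

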### 3.7 Concomitant Treatments

All participants are encouraged to inform their GPs and CPs about their participation in this study upon discharge from hospital to ensure a safe delivery of healthcare services. Throughout the study, participants will be able to take any medication as required, except for smoking cessation medications. Use of concomitant medication will be recorded at each of the study follow-ups and checked for potential interactions. The use of other smoking cessation medications including other forms of NRTs (i.e. patches or gums) is strongly discouraged during the course of the study to ensure patient safety. If a participant uses other smoking cessation medication during the study period, an appropriate record of this will be maintained. Their results will still be included in the primary and secondary analyses, however, sensitivity analysis will be performed by excluding them from the primary analysis.

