## 4. Statistical Considerations

### 4.1 Sample Size

To show a difference of 15% in continuous abstinence between study arms (based on continuous abstinence rate of 23% in varenicline trials) at the 5% level of significance with 80% power, we will need 160 subjects per arm. i.e. 320 participants in total from the six hospitals, , 160 in each of the study arms. The primary analysis will be intention to treat (ITT) and lost to follow-up participants will be regarded as smokers.

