| Thoughts of self-harm             |                     |         |                     |         |                       |         |                       |         |                      |         |
| Changes in mood or behaviour      |                     |         |                     |         |                       |         |                       |         |                      |         |
| Other**                           |                     |         |                     |         |                       |         |                       |         |                      |         |

\*\*Other includes: hiccups; dizziness; sweats; palpitations; rashes; metallic taste; etc.

**Per protocol analysis:** All randomized participants who took at least one dose of the treatment medications will be included in the per protocol analysis.

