**Table 6: Smoking abstinence rates by treatment groups from 2 weeks to 3, 6 and 12 months – Per protocol analysis**

| Outcome                                         | Intervention
N =
n (%) | Control
N =
n (%) | Odds ratio (95% CI) |
|-------------------------------------------------|------------------------------|-------------------------|---------------------|
| Smoking abstinence at 3-months           |                              |                         |                     |
| Self-reported prolonged abstinence              |                              |                         |                     |
| Self-reported 7-day point prevalence abstinence |                              |                         |                     |
| Smoking abstinence at 6-months           |                              |                         |                     |
| Biochemically verified prolonged abstinence     |                              |                         |                     |
| Self-reported prolonged abstinence              |                              |                         |                     |
| Self-reported 7-day point prevalence abstinence |                              |                         |                     |
| Smoking abstinence at 12-months          |                              |                         |                     |
| Biochemically verified prolonged abstinence     |                              |                         |                     |
| Self-reported prolonged abstinence              |                              |                         |                     |
| Self-reported 7-day point prevalence abstinence |                              |                         |                     |

Note: Deceased participants at each time-point will be excluded from those specific analyses.

Quitline sessions attended will be compared between the treatment groups using a  $\chi^2$  test.

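### The SAP's per-protocol set uses the protocol's safety-set rule, so Table 6 is a treated-set analysis and the promised per-protocol support for the primary endpoint is missing

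*Combined protocol and SAP*

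**What the plan says.** Protocol Section 4.2 (Data Analysis) names two analysis sets besides ITT. The first serves to back up the primary result and is described as supportive: "an analysis will also be conducted on the per protocol set, which excludes patients with any major protocol deviations". The second is for safety: "All randomised participants who take at least one dose of the treatment medications will be included in the safety analysis".

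The SAP paragraph headed Per protocol analysis, directly above Table 6, reads: "All randomized participants who took at least one dose of the treatment medications will be included in the per protocol analysis". It names no exclusion for deviations. The table it introduces is titled "Smoking abstinence rates by treatment groups from 2 weeks to 3, 6 and 12 months – Per protocol analysis", and the only exclusion noted beneath it is "Deceased participants at each time-point will be excluded from those specific analyses".

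**The concern.** The SAP puts the per-protocol label on the rule that the protocol uses for safety, in nearly the same words. Someone who took one tablet and stopped, used another cessation product throughout, or turned out to be ineligible would stay in Table 6.

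A per-protocol analysis is meant to estimate the effect among participants without major deviations. A set that removes only the never-dosed estimates something very close to ITT. Table 6 is also the only alternative-set analysis of abstinence laid out in the SAP. If it agrees with Table 2, readers may take that as evidence that the result holds in people who followed the protocol, which the table would not have examined.

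**Working it through.** **1. The definitions side by side**

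| Item | Protocol Section 4.2 | SAP |
|---|---|---|
| Per-protocol set | Removes major deviators | Randomised, at least one dose |
| Safety set | Randomised, at least one dose | No population stated for adverse events |
| Outcomes in the per-protocol analysis | Primary endpoint | Table 6: the same eight rows as Table 2 (2 at 3 months, 3 at 6 months, 3 at 12 months) |
| Deceased participants | Excluded | Excluded from Tables 2 and 6 alike |

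The SAP's per-protocol cell matches the protocol's safety cell, not its per-protocol cell. No redaction, broken table or amendment log accounts for this.

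**2. Who leaves between Table 2 and Table 6**

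- Table 2 (ITT) = randomised − deceased.
- Table 6 as the SAP defines it = randomised − deceased − never dosed.
- Table 6 as the protocol defines it = randomised − deceased − major deviators.

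Under the SAP, the two tables differ only by surviving participants who never took a dose. That group is probably small. Recruits are inpatients who want to quit and accept medication (Section 3.1). They receive both products straight after randomisation and are told to begin promptly (Section 3.5.3). First dosing is not described as observed, so this is an inference. The SAP also refers to the treatment medications collectively, so a single varenicline tablet can qualify although the arms differ only in the lozenge.

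**3. The plan's own figure**

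This point disputes no number, but the illustrations below use the planning rates in Section 4.1: 23% in the control arm and 23% + 15% = 38% in the intervention arm, two-sided 5%, 80% power.

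- Mean rate = (0.23 + 0.38)/2 = 0.305.
- √(2 × 0.305 × 0.695) = 0.6511; √(0.23 × 0.77 + 0.38 × 0.62) = 0.6424.
- n = (1.960 × 0.6511 + 0.8416 × 0.6424)² / 0.15² = 146.7, so 147 per arm.
- With continuity correction: (146.7/4) × [1 + √(1 + 4/(146.7 × 0.15))]² = 159.8, so 160 per arm.

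The stated 160 per arm is reproduced.

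**4. How far Table 6 could move from Table 2 (assumed inputs)**

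Assume 5% of each arm is never dosed.

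- If they abstain at the same rate as everyone else, the rates do not change. Odds ratio = (0.38/0.62)/(0.23/0.77) = 2.05.
- If all of them count as smokers, the rates become 0.23/0.95 = 24.2% and 0.38/0.95 = 40.0%. Odds ratio = (0.400/0.600)/(0.242/0.758) = 2.09.

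In both cases Table 6 nearly repeats Table 2.

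**5. How different a set with deviators removed could be (assumed inputs)**

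Power = Φ[(0.15√n − 1.960 × 0.6511)/0.6424], with rates held at 23% and 38% and no continuity correction.

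| Assumed exclusion per arm | n per arm | Power |
|---|---|---|
| 0% | 160 | 83% |
| 5% | 152 | 81% |
| 20% | 128 | 74% |
| 40% | 96 | 62% |

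The 0–5% rows stand for never-dosed exclusions and the 20–40% rows for major deviations. None of these percentages is in the documents. They show only that the two rules can give quite different sets.

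**The case against.** The strongest reply is that little depends on Table 6. The protocol calls the analysis supportive. The primary analysis is ITT, with missing or unverified participants counted as smokers, and no primary estimate, alpha or sample size draws on the per-protocol set. This stands, and it limits how serious the point is.

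A second reply is that the protocol has other checks on the primary result: multiple imputation (Section 4.2), a CO cut-off below 5 ppm (Section 3.9.2) and, for users of other cessation medication, "sensitivity analysis will be performed by excluding them from the primary analysis" (Section 3.7). The SAP text does not repeat these, but it does not withdraw them either. A reader might infer that the plan has no test of robustness at all. The protocol does not support that reading. What is missing is the per-protocol analysis specifically.

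Three further inferences also go too far:

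- **A count of wrongly retained participants.** Assuming 2–5% never dosed and 20–40% with major deviations gives 304–314 against 192–256 of 320, a gap of 48 to 122. That gap cannot be presented as people whom the protocol excludes. The rates are assumed, and the protocol never defines a major deviation.
- **Non-use of lozenges as a deviation.** The lozenge instructions in Section 3.5.3 tie use to craving. A participant with no cravings who takes none has followed them. Removing such people would select on a post-randomisation response closely tied to abstinence.
- **Early stopping as an automatic deviation.** Sections 3.10 and 6 provide for discontinuation, and people who relapse may stop treatment. A threshold could therefore select abstainers.

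**Conclusion.** The conflict between the SAP paragraph and protocol Section 4.2 is real and does not depend on any assumed rate. Table 6 as specified is a treated-set or modified ITT analysis, and it does not deliver the per-protocol support for the primary endpoint that the protocol promises. That it will nearly repeat Table 2 is probable rather than certain, because it rests on few participants going undosed. With an assumed 5% never dosed in each arm, the planning odds ratio moves from 2.05 to at most 2.09 across the two cases worked.

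The number of participants affected is unknown. The consequence is confined to a supportive analysis and its label. The SAP definition should be corrected before the analysis is run, but nothing here casts doubt on the ITT primary result.

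**What to change.** 1. In the SAP, rename the one-dose set the treated or safety set. If Table 6 keeps that set, title it modified ITT.
2. Run the per-protocol analysis of the primary endpoint on "the per protocol set, which excludes patients with any major protocol deviations", as Section 4.2 states.
3. Because the protocol leaves major deviations undefined, write the list and fix it before outcomes are seen by arm. Build it from planned data, for example ineligibility (screening and baseline records, Sections 3.3 and 3.4), use of other cessation medication (Section 3.7, SAP Table 8), and wrong treatment dispensed where this was recorded. The documents describe no specific log for the last item.
4. Do not list non-use of the as-needed lozenges. Include early stopping only with a justification written in advance.
5. Label the analysis supportive and non-randomised.
6. Reconcile the outcomes: either limit the per-protocol table to the primary endpoint, as the protocol does, or state that the SAP extends it to all eight rows of Table 6.

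The cost is SAP wording and a short deviation review, with no new data collection. The downside is a smaller set, a wider confidence interval and possible selection bias, all within a supportive analysis.
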